**Abstract:**

The agri-food supply chain is a relevant contributor to the Italian economy but shows a high incidence of occupational injuries and musculoskeletal disorders, such as lower back pain. Repetitive manual handling and biomechanical overload highlight the need for a prevention-oriented, system-level assessment. This protocol aims to implement a harmonized One Health approach procedure for the multidimensional evaluation of food supply chain workers in real-world settings. The protocol integrates bioelectrical impedance vector analysis (BIVA), nutritional parameters, quality-of-life and psychological measures, and assessments of systemic oxidative stress and systemic serotonin levels. Data from active workers will be compared with those from sedentary individuals. The study will evaluate whether BIVA profiles differ between these groups and examine how the additional indicators contribute to a multidimensional well-being framework. By operationalizing an integrated One Health approach that bridges nutritional, psychological, and biomarker domains, this protocol is designed to guide targeted preventive and educational strategies and inform evidence-based occupational and public health policies across the food supply chain. Trial registration: NCT06896877 (ClinicalTrials.gov), 26 March 2025.

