### 3.1. Anamnestic and Lifestyle Information

Once enrolled, the following data will be recorded for each participant: demographic and general health information and smoking habits; use of medications, supplements and nutraceuticals; and type of work and number of working hours per day, week and year and active breaks during work.

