### 3.6. Sample Size and Statistical Analysis

This is an exploratory, two-group study (active workers vs. sedentary workers). We planned a total sample of 40 participants (≈20 per group). A priori calculations were performed with G*Power (v3.1.9.7) to inform feasibility for a two-group multivariate comparison approximating Hotelling’s T^2^ (implemented as a MANOVA with two dependent variables, R/H and Xc/H). Under conventional assumptions (two-sided α = 0.05; target power ≈ 0.80; small-to-moderate multivariate effect), a sample size of 35 is typically adequate; therefore, we set N = 40 to accommodate measurement variability and potential attrition while maintaining balanced groups. Although the sample size calculation is fixed to the primary bioimpedance outcomes, the nutritional, biochemical, and psychological variables will be treated as exploratory secondary outcomes. For these, the study aims to estimate effect sizes and variability and to evaluate feasibility rather than to achieve confirmatory statistical power.

Raw R and Xc will be standardized by height (H) to obtain R/H and Xc/H. For each group, we will compute the mean vector and its 95% confidence ellipse on the RXc plane. The primary comparison between active vs. sedentary workers is the displacement of the mean impedance vector assessed with two-sample Hotelling’s T^2^ (reporting T^2^, *p*-value, Mahalanobis distance, and 95% CI for the mean-vector difference). Visualization will include the RXc-mean graph with group ellipses. Covariate-adjusted MAN(C)OVA models will be used as sensitivity analyses to assess robustness. In addition to age and sex—variables inherently related to BIVA interpretation—analyses will adjust for occupational factors (e.g., type of work tasks, years in role, ergonomic load) and lifestyle habits (e.g., smoking, alcohol consumption, physical activity outside work), which may influence hydration, body composition, metabolic state, or psychological indicators. Contemporary reference/tolerance ellipses for interpretation will follow Campa et al. [52] or the most appropriate sex-/age-specific set for our sample.

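### The robustness models for active versus sedentary workers adjust for work tasks and ergonomic load, which probably define or closely track the grouping, so a shrunken adjusted difference would not show that the primary result is fragile

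*Protocol article*

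**What the plan says.** Section 3.6 of the protocol article sets up the comparison: "This is an exploratory, two-group study (active workers vs. sedentary workers"). The abstract describes it in similar terms: "Data from active workers will be compared with those from sedentary individuals". Section 1.2 speaks of sedentary and physically active workers in the food supply chain. None of these places says how a worker is put into one group or the other.

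The primary test is the unadjusted two-sample Hotelling's T² on R/H and Xc/H. Covariate-adjusted MAN(C)OVA models are sensitivity analyses meant to show robustness. Besides age and sex, "analyses will adjust for occupational factors (e.g., type of work tasks, years in role, ergonomic load) and lifestyle habits", the last illustrated by smoking, alcohol and physical activity outside work. That makes eight named covariates.

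The work information listed in Section 3.1 is "type of work and number of working hours per day, week and year and active breaks during work". Section 4 says that the group contrast will be read without causal claims.

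**The concern.** A robustness model should estimate the same contrast as the primary analysis with confounding reduced. Here two of the named covariates look like the contrast itself. The abstract and Section 1.1 motivate the study by manual handling and biomechanical overload at work, and Section 3.1 records the type of work. On that reading, what a worker does and how heavy it is are what separate an active worker from a sedentary one, or follow directly from it. Holding them fixed asks whether active and sedentary workers differ when their tasks and load are the same. That is another question, and one that 40 people can hardly answer.

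At stake is the interpretation. If the groups truly differ, the adjusted difference is expected to shrink and its interval to widen. Under the plan's labelling, this would be read as the primary finding failing its robustness check.

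**Working it through.** **1. The plan's own figure.** Inputs from Section 3.6: "two-sided α = 0.05; target power ≈ 0.80; small-to-moderate multivariate effect"; "a sample size of 35 is typically adequate"; "We planned a total sample of 40 participants (≈20 per group"); "implemented as a MANOVA with two dependent variables, R/H and Xc/H". For two equal groups and two outcomes, power comes from a noncentral F with 2 and N − 3 degrees of freedom and noncentrality λ = D² × n₁n₂/N, where D is the Mahalanobis distance between the mean vectors. With N = 35, 80% power needs D = 1.10 (f² = D²/4 = 0.30). The plan states no numerical effect, so its 35 cannot be reproduced from its own inputs. Whether 35 fits the verbal description of the effect is a separate matter. Here an effect is needed only as a starting point, and D = 1.02 is used because it gives 80% power at the planned N = 40:

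λ = 1.02² × (20 × 20)/40 = 1.0404 × 10 = 10.40; degrees of freedom 2 and 37; power 80%.

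**2. Loss of precision from one overlapping covariate.** Suppose the covariate has correlation r with group and the adjusted effect stays at D. The noncentrality becomes λ(1 − r²), the variance inflation is 1/(1 − r²), and the degrees of freedom are 2 and 36. The values of r are assumptions, since the document gives none.

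| r with group | Variance inflation | λ(1 − r²) | Power |
|---|---|---|---|
| 0.3 | 1.10 | 9.47 | 76% |
| 0.5 | 1.33 | 7.80 | 67% |
| 0.7 | 1.96 | 5.31 | 49% |
| 0.8 | 2.78 | 3.75 | 36% |
| 0.9 | 5.26 | 1.98 | 21% |

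The pattern does not depend on the choice of D. With D = 1.10, N = 40 and eight covariates that together explain a share R² of group membership, power falls from 86% unadjusted to 73% at R² = 0.25, 54% at 0.50, 30% at 0.75 and 14% at 0.90.

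**3. Attenuation.** Step 2 holds the effect fixed, but overlap also shrinks it. In a simulation of 3,000 studies of 40 people per scenario with one outcome, group is a median split of occupational load and load drives the outcome (outcome = 0.6 × load + 0.8 × noise). The unadjusted group difference averages about 0.93. In this table the correlation is with the underlying load, not with the group indicator, so its scale differs from step 2.

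| Covariate's correlation with load | Adjusted group difference |
|---|---|
| 0 | 0.93 |
| 0.5 | 0.83 |
| 0.7 | 0.68 |
| 0.9 | 0.36 |
| 0.95 | 0.19 |
| 1.0 | about 0 |

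The unadjusted difference is genuine in every row, so the shrinkage says nothing against it.

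**4. The limit.** If group is a function of the task category, its indicator is a linear combination of the task terms and the group effect cannot be estimated at all.

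**The case against.** Several points on the other side stand and set the limits of this one.

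- **The grouping rule is not in the article.** That tasks and load make a worker active or sedentary is an inference. A seated worker could carry a high ergonomic load, and tasks can vary within a group. A reader might infer that at least one listed covariate must be the exposure on any reading. The documents support likely overlap, not identity.
- **The activity covariate is activity outside work.** If groups follow the job, it is an ordinary confounder and belongs in the model. It becomes part of the exposure only if groups follow overall activity. Age, sex, smoking and alcohol are not the exposure on any reading.
- **Vanishing is too strong.** A reader might infer that a true difference will disappear after adjustment. At correlations of 0.3 to 0.5 with group the loss of power is modest. Covariates that explain outcome variance, as age and sex may, would recover some of it.
- **Collection.** A reader might infer from Section 3.1 that ergonomic load, years in role and outside activity are not recorded. Section 2.1 announces surveys that include occupational health, and Section 3.2.3 collects alcohol intake, so Section 3.1 is not the full list.
- **The covariates are examples and the models are plural.** An age-and-sex variant is compatible with the text. Even so, tasks and ergonomic load are named, and the text says the analyses will adjust for them.
- **Exploratory study, no causal claims.** This limits the harm but does not cure it. The adjusted contrast still answers a different question and is still labelled a check of robustness.

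**Conclusion.** The point holds as a fault in the choice of covariates for the sensitivity models. It does not touch the unadjusted primary Hotelling's T². On the natural reading that groups follow activity at work, the models named as robustness checks condition on variables that define the exposure or closely track it. A smaller or null adjusted difference would then be expected even when the primary result is true, and could not be taken as evidence of fragility.

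The size depends on an overlap that the documents do not give. From 80% unadjusted power, one covariate leaves about three quarters at a correlation of 0.3 with group, about half at 0.7 and about a fifth at 0.9. The documents do not support the stronger statement that adjustment removes the exposure, because that needs near-complete overlap. The change should be made, but the study does not fail without it.

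**What to change.** In Section 3.6, state that group is assigned from the job recorded at enrolment, before the bioimpedance result is read. Remove type of work tasks and ergonomic load from the robustness model. Limit that model to age, sex and one or two genuine confounders, for example smoking. Physical activity outside work may be one of them only if the groups are defined by activity at work. Report tasks and ergonomic load descriptively by group, or in a separate model labelled explanatory and not offered as a check on the primary result.

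The cost is a change of wording. The downside is fewer adjusted variants to report.

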Standardized phase angle (SPhA), adjusted to sex- and age-specific references, will be analyzed as a continuous endpoint. The primary comparison (active vs. sedentary) will use a two-sample t-test. A sensitivity ANCOVA adjusting for BMI (and other prespecified covariates, if applicable) will assess robustness. The proportion of participants with SPhA ≤−1.65 (≈5th percentile) will be compared between groups using χ^2^ or Fisher’s exact test (reporting risk ratio and 95% CI). Secondary exploratory outcomes, deriving from nutritional, biochemical, and psychological domains’ assessment, will be analyzed with χ^2^/Fisher for categorical variables and t-test/Mann–Whitney for continuous variables depending on normality (assessed with Shapiro–Wilk). Effect sizes with 95% confidence intervals will be reported. Age will be included as a continuous covariate in sensitivity MAN(C)OVA and ANCOVA models. Exploratory analyses will also examine age-related associations with bioimpedance, psychological, and biomarker measures.

Exploratory associations among nutritional indicators (SPhA), bioimpedance parameters, oxidative-stress markers, serotonin, and psychological measures will be examined using Pearson or Spearman coefficients as appropriate. No directional hypotheses are pre-specified for these exploratory analyses; findings will be interpreted as hypothesis-generating.

No missing data are expected because all measurements will be collected during supervised in-person sessions. Data completeness will be verified at the time of assessment. If unexpected missingness occurs, analyses will follow a complete-case approach and the extent of missing data will be reported.

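### With about one expected case per group, the risk ratio fixed for low SPhA is a poor effect measure; a risk difference with a score-type interval can always be reported (minor point, exploratory measure)

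*Protocol article*

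**What the plan says.** All the relevant text is in section 3.6 of the protocol article (Sample Size and Statistical Analysis).

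- **Sample:** "We planned a total sample of 40 participants (≈20 per group"). The calculation behind it is tied to the primary bioimpedance variables R/H and Xc/H and does not cover SPhA. The total was raised from 35 to 40: "we set N = 40 to accommodate measurement variability and potential attrition while maintaining balanced groups".
- **Main SPhA analysis:** "Standardized phase angle (SPhA), adjusted to sex- and age-specific references, will be analyzed as a continuous endpoint", by two-sample t-test with a sensitivity ANCOVA.
- **Added binary analysis:** "The proportion of participants with SPhA ≤−1.65 (≈5th percentile) will be compared between groups". The test is chi-square or Fisher's exact test, and the effect measure is given in the same sentence: "reporting risk ratio and 95% CI".

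The article names no interval method, no rule for a group without cases and no expected rate of low SPhA in these workers. Section 1.2 lists SPhA among the secondary exploratory aims.

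**The concern.** A z-score cut-off at about the 5th percentile picks out, by construction, about one person in twenty of the reference population. With about twenty people per group, the numerator of each proportion is expected to be about one. A ratio of two such counts is zero or infinite whenever one group has no case, and has no value at all when neither has one.

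What is at stake is the usefulness of one reported estimate. Section 3.6 says that the secondary outcomes serve to estimate effect sizes and variability, and section 4 promises estimates with their uncertainty for all variables and names low SPhA as a possible marker of workers who could benefit from support. A measure with a sizeable chance of having no finite, non-zero value serves that purpose badly. It could also leave the team to choose a continuity correction or another measure once the counts are known.

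**Working it through.** **Inputs, all from section 3.6:** n = 20 per group; cut-off SPhA ≤ -1.65; reference rate p of about 5%; effect measure risk ratio with 95% CI. One assumption is added: both groups have the same true rate p. It is varied below because the article states no rate for these workers.

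**1. The plan's own figure.** For a standard normal score, Φ(-1.65) = 0.0495. This agrees with the stated 5th percentile, so the cut-off itself is correct.

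**2. Expected cases per group.** 20 × 0.05 = 1.0.

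**3. Chance that a group has no case.** q = (1 - p)^20 = 0.95^20 = 0.358.

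**4. Chance that the ratio is not a finite, non-zero number.**

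- Zero: q(1 - q) = 0.358 × 0.642 = 0.230
- Infinite: (1 - q)q = 0.230
- Undefined (0/0): q² = 0.129
- Total: 1 - (1 - q)² = 1 - 0.642² = 0.588

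A simulation of 1,000,000 studies gave 0.588 for the total.

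**5. Dependence on the rate and group size.**

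| Rate, group 1 / group 2 | n per group | At least one empty group | Both empty |
|---|---|---|---|
| 2.5% / 5% | 20 / 20 | 74.5% | 21.6% |
| 5% / 5% | 20 / 20 | 58.8% | 12.9% |
| 5% / 5% | 17 / 18 | 64.9% | 16.6% |
| 6% / 6% | 20 / 20 | 49.6% | 8.4% |
| 5% / 10% | 20 / 20 | 43.7% | 4.4% |
| 10% / 10% | 20 / 20 | 22.8% | 1.5% |
| 15% / 15% | 20 / 20 | 7.6% | 0.2% |

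With equal groups of 20, the total passes 50% only when the common rate is below about 6.0%.

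**6. Width of the interval when the ratio can be computed (log-Wald).** SE of log RR = √(1/a - 1/20 + 1/b - 1/20), where a and b are the case counts.

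- 1 vs 1: SE = √1.9 = 1.378; RR 1.0, 95% CI exp(±1.96 × 1.378) = 0.07 to 14.9
- 3 vs 1: RR 3.0, 95% CI 0.34 to 26.5

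**7. The alternative.** The Newcombe interval for the risk difference combines the two Wilson intervals and exists for every table.

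- 0 vs 0: difference 0, 95% CI -0.16 to 0.16
- 2 vs 0: difference 0.10, 95% CI -0.08 to 0.30

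**The case against.** A reader might go further and infer that the planned measure will usually not exist. The documents do not support that.

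- The majority depends on both groups sitting at the reference rate. No rate is stated for these workers, and section 2.2 keeps participants with chronic conditions in the study, so a higher rate is possible. At 10% in both groups the chance of an empty group is only 23%.
- Zero is an estimate, and the article does not commit to the log-Wald interval. A score interval for the ratio exists with one empty group: 0/20 vs 2/20 gives 0 to about 1.8, and 2/20 vs 0/20 gives about 0.56 to infinity. For 1 vs 1 the score interval is about 0.11 to 9.2. Only 0/0, about 13% at the reference rate, yields nothing.

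Two other strong readings also fail. Chi-square would be unsuitable with counts this small, but the plan already allows Fisher's exact test. Low power to detect a difference in this proportion is no defect either: the study is exploratory, its sample size was never meant to cover this comparison, and inference on continuous SPhA is already planned.

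Finally, interval methods and zero-cell rules are often left to a statistical analysis plan. The article's data availability statement mentions one, and it is not shown, so their absence from the article is not the fault.

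All of this stands and narrows the point. What remains is that the article itself fixes the ratio as the effect measure, next to a cut-off and a group size that imply about one case per group. Score intervals for the ratio stay very wide or one-sided at these counts.

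**Conclusion.** The point holds in a limited form. At the article's own reference rate in both groups of 20, the risk ratio is zero or infinite in about 46% of studies and undefined in about 13%, together 59%. The total is 50% at a common rate of 6% and 23% at 10%. When the ratio can be computed from one or a few cases, its interval spans roughly two orders of magnitude.

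The percentages assume independent participants, the planned group sizes and a stated common rate; the true rate in these workers is unknown. The importance is minor: one exploratory secondary measure is affected, and neither the primary Hotelling's T² comparison nor the continuous SPhA analysis depends on it.

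**What to change.** Change the sentence in section 3.6 on the low-SPhA proportion as follows:

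- Report the number of cases and the denominator in each group, and the risk difference with a Newcombe or Miettinen-Nurminen 95% CI, in place of the risk ratio. Alternatively, keep the ratio as a secondary measure, reported only when both groups have cases.
- Use Fisher's exact test for this comparison.
- State that this proportion is descriptive and that inference on SPhA rests on the continuous analysis already planned.

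The cost is one sentence, with no new data and no change to the sample size. The downside is that a relative measure, which some readers find easier to compare across studies, is lost or moved to second place.

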#### 3.2.3. Eating Habits Questionnaire

The participant will also complete a survey on dietary habits, including daily water intake and consumption of other beverages (including alcoholic drinks), adherence to the Mediterranean diet (weekly intake of olive oil, nuts, cereals and whole grains, vegetables, meat, dairy products, processed and industrial foods, chocolate, coffee and tea), as well as the presence of specific dietary regimens and eating habits.

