#### 3.3.2. Assessment of Biomarker of Systemic Oxidative Status

The systemic oxidative status will be analyzed through the following analyses on an integrated analytical photometer (Diacron International S.r.l., Grosseto, GR, Italy).

Total hydroperoxides colorimetric determination of ROMs (Reactive Oxygen Metabolites) (d-ROMs test; Diacron International S.r.l., Grosseto, GR, Italy). In the d-ROMs test, ROMs (primarily hydroperoxides) contained in the biological sample, close to iron, generate alkoxyl and peroxyl radicals, according to the Fenton’s reaction. The radicals, reacting with a chromogenic mixture, oxidize it and transform it into a photometrically measurable coloured derivative. The measurements are reported in arbitrary units (UCARR), where 1 UCARR corresponds to 0.08 mg/100 mL of hydrogen peroxide [40]. Values between 250 and 300 UCARR fall within the normal reference range; 301–320 UCARR are classified as borderline; 321–340 UCARR indicate low oxidative stress; 341–400 UCARR indicate moderate oxidative stress; 401–500 UCARR reflect high oxidative stress; and values exceeding 500 UCARR correspond to very high oxidative stress (Diacron International S.r.l., Grosseto, GR, Italy). The reproducibility of the test reported as CV% is 1.72.The total biological antioxidant capacity (BAP-Test; Diacron International S.r.l., Grosseto, GR, Italy) quantifies the overall pool of endogenous (e.g., bilirubin, uric acid, proteins) and exogenous (e.g., ascorbate, tocopherols, carotenoids, flavonoids) plasma components capable of exerting antioxidant activity and neutralizing reactive radical species. In the BAP test, the biological antioxidant potential of plasma barrier is based on the ability of all antioxidants active to reduce a coloured solution of ferric ions (Fe^3+^) to ferrous ions (Fe^2+^), resulting in a decolouration of the solution that is photometrically detectable. Reference values in µmol/L that are >2200 are intended as “normal antioxidant status”, 2200–2000 are considered a “border line antioxidant status, 2000–1800 are interpreted as “at slight antioxidant deficiency status”, 1800–1600 as “deficiency of antioxidant status”, <1600 as a “high and very high deficiency of antioxidant status” condition (Diacron International S.r.l., Grosseto, GR, Italy). The reproducibility of this test expressed as CV% is 2.32.Calculation of the OSI index to assess the relative antioxidant capacity, namely, the antioxidant capacity normalized for total circulating hydroperoxides. This index is the antioxidative/oxidative stress ratio assessed by the ratio equation: BAP/d-ROMs. We refer to this ratio as the OSI index, which reflects the system’s potential antioxidant capacity [44]. A threshold value of 7.3 was adopted for the BAP/d-ROMs ratio; values below this cut-off were classified as “oxidised,” whereas values equal to or above 7.3 were considered “reduced” [45].

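### Ordered categories share the chi-square/Fisher rule with nominal ones, so any secondary outcome held only as ordered classes is compared without using its order (minor; one-sentence repair)

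*Protocol article*

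**What the plan says.** Section 3.6 gives one rule for the secondary exploratory outcomes in the nutritional, biochemical and psychological domains: chi-square or "Fisher for categorical variables and t-test/Mann–Whitney for continuous variables", with the choice inside each pair left to circumstances (Shapiro–Wilk for the continuous pair). Mann–Whitney is tied to continuous variables. No test is named for ordered categories.

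The article defines several ordered classifications:

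- **d-ROMs (section 3.3.2):** six bands running from normal through borderline upward, for example "321–340 UCARR indicate low oxidative stress; 341–400 UCARR indicate moderate oxidative stress", then "401–500 UCARR reflect high oxidative stress; and values exceeding 500 UCARR correspond to very high oxidative stress".
- **BAP (section 3.3.2):** five bands, from normal antioxidant status to high or very high deficiency.
- **PNI (section 3.3.1):** three risk classes.
- **Diet (section 3.2.3):** items on "weekly intake of olive oil, nuts, cereals and whole grains, vegetables, meat, dairy products" and other foods. The response format is not given.

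On size, section 3.6 states: "We planned a total sample of 40 participants (≈20 per group"). It adds that the secondary outcomes serve to estimate effect sizes and variability, not to reach confirmatory power, and that effect sizes with 95% confidence intervals will be reported.

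**The concern.** Pearson chi-square and Fisher's exact test treat class labels as names. With k classes in two groups they spread their sensitivity over k − 1 degrees of freedom: 2 for PNI, 4 for BAP, 5 for d-ROMs. If one group simply tends towards the worse classes, a rank or trend test puts the same information into a single degree of freedom and detects the shift more often.

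There is also an estimation side. The article promises effect sizes with intervals, but for a table with three or more ordered classes neither named test comes with a directional measure. The only one specified for a class comparison is the risk ratio for the binary SPhA cut-off. With 40 participants there is little information to give away.

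**Working it through.** **Plan's own figure.** The article gives no power figure for categorical secondary outcomes. Its only calculation, under which "a sample size of 35 is typically adequate", concerns the primary Hotelling comparison. It gives no numeric effect size, and it has no bearing on this point.

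**Inputs from the article.** 20 per group (section 3.6); class counts 6, 5, 3 and 2 (sections 3.3.1, 3.3.2 and 3.6). Two-sided α = 0.05 is stated only for the primary comparison and is borrowed here.

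**Assumed, because the article gives none.** Classes evenly filled in the reference group; a proportional-odds shift with odds ratio 3. Four classes are included for illustration.

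**Step 1: class shares after the shift, six classes.** Reference cumulative shares are 1/6 to 5/6, so the cumulative odds are 0.2, 0.5, 1, 2 and 5. Dividing by 3 gives 0.067, 0.167, 0.333, 0.667 and 1.667. As cumulative shares these are 0.0625, 0.1429, 0.25, 0.40 and 0.625. The class shares are therefore 0.0625, 0.0804, 0.1071, 0.15, 0.225 and 0.375, against 0.1667 each in the reference group. The probability of superiority is 0.67.

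**Step 2: large-sample check.** Noncentrality λ = n Σ (p − q)² / (p + q), with n = 20 per group.

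- Six classes: the sum is 0.180, so λ = 3.60. Power is 0.26 on 5 df. On 1 df it is P(Z > 1.96 − √3.60) = P(Z > 0.06) ≈ 0.475.
- Three classes: shifted shares 0.143, 0.257 and 0.600; the sum is 0.162, so λ = 3.24. Power is 0.35 on 2 df and 0.44 on 1 df.

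**Step 3: simulation.** 200,000 tables per row, Pearson chi-square without correction against the tie-corrected Mann–Whitney test, odds ratio 3.

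| Classes | Chi-square | Rank test | Relative loss | Null rejection (chi-square / rank) |
|---|---|---|---|---|
| 2 | 0.37 | 0.37 | none | 0.042 / 0.042 |
| 3 | 0.35 | 0.44 | 21% | 0.050 / 0.049 |
| 4 | 0.30 | 0.46 | 34% | 0.049 / 0.050 |
| 5 | 0.27 | 0.47 | 44% | 0.046 / 0.049 |
| 6 | 0.24 | 0.48 | 51% | 0.043 / 0.049 |

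**Step 4: Fisher instead of chi-square.** The exact Fisher–Freeman–Halton test against a permutation rank test, odds ratio 3, even classes, 2,500 tables per setting:

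- six classes: 0.27 against 0.48, a loss of 43%;
- five classes: 0.28 against 0.46, a loss of 39%;
- three classes: 0.32 against 0.40, a loss of 20%.

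**Step 5: sensitivity to the assumptions (chi-square against rank test).**

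- Six even classes: 0.11 against 0.23 at odds ratio 2; 0.37 against 0.67 at 4; 0.59 against 0.86 at 6. The relative loss falls from about half to about a third.
- Six classes with skewed shares (0.30, 0.20, 0.15, 0.20, 0.10, 0.05), odds ratio 3: 0.23 against 0.48.
- Three classes with skewed shares (0.80, 0.12, 0.08), odds ratio 3: 0.26 against 0.35.

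**The case against.** **The variables with most classes do not depend on the class table.** d-ROMs and BAP are measured numerically and PNI is a computed score, so all three can go to the t-test/Mann–Whitney branch. The article presents their bands as reference ranges and nowhere says that the bands will be compared between groups. The one class comparison tied explicitly to chi-square/Fisher, SPhA at or below −1.65, is binary. This stands, and it is the main reason the point is small.

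**The remaining candidate is conditional.** Dietary intake could be recorded in servings per week, which Mann–Whitney would handle. The Data Availability statement says the questionnaires are available on request, so the format is unknown here. This stands too: the dietary case holds only if answers are in steps, and the six-class figure cannot be carried over to it.

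**It is a matter for the statistical analysis plan.** The same statement says such a plan exists, and it may refine the rule. But the article itself fixes which tests go with which type of variable, and read as written, ordered categories fall under chi-square/Fisher.

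**An omnibus test may be intended.** Section 4 anticipates heterogeneous patterns and weak, non-directional associations. Chi-square is the more sensitive choice if differences are not monotone. This is fair, and it is the price of the change.

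**Expected counts.** A reader might infer that chi-square is invalid with six classes, because the average expected count is 20/6 = 3.3. The documents do not support that as a fault: Fisher is offered alongside, and in the simulation chi-square rejected 4.3% of the time under no difference.

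**Effect sizes.** A reader might also infer that only a bare p-value would be reported. The article promises effect sizes with 95% confidence intervals. What it does not name is a measure suited to ordered classes.

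**Conclusion.** The point holds in a limited form. The stated rule does not distinguish ordered from nominal categories, and ordered classes analysed under it would be compared without using their order. At 20 per group and an assumed odds ratio of 3 with evenly filled classes, power is about 0.35 instead of 0.44 with three classes and 0.24 instead of 0.48 with six.

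It would be tempting to say that all categorical secondary outcomes lose up to half their power. That is not supported. A loss of half needs about six classes, Pearson chi-square and a modest one-directional shift. Three classes lose roughly a fifth to a third, depending on class shares and effect size, and two classes lose nothing. The unavoidable loss is confined to outcomes held only as ordered categories, chiefly dietary answers if they are recorded in steps.

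Effect sizes and class shares are assumptions. The outcomes are exploratory with no power target, and the primary Hotelling comparison is unaffected. This is a cheap improvement, not a defect that threatens the study.

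**What to change.** Amend the sentence on secondary outcomes in section 3.6 along these lines:

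*Chi-square or Fisher's exact test for nominal and binary variables; tie-corrected Mann–Whitney (or a linear trend test) for ordered categories, reporting the probability of superiority or a common odds ratio with 95% CI; t-test or Mann–Whitney for continuous variables. For d-ROMs, BAP and PNI the continuous values are the main comparison and the bands are descriptive.*

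If the dietary items are answered in steps, list them as ordered.

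The cost is one or two sentences and no new data. The statistical price is less power against differences that do not run in one direction across the classes, which tabulating the class counts by group would still show.
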